**FIGURE 2 F2:**
[figure not shown]
Data processing and analysis workflow. **(A)** First, the lesion will be manually defined on T_2_-FLAIR images. **(B)** Two complementary methods, one based on lesions and the other on the connectome, will be used to characterize brain damage. To compute lesion-based damage (top row), the brain atlas and each individual’s lesion mask will be aligned with each individual’s native T_1_ space. The gray matter regions will be divided into regions of interest (ROIs) according to the atlas. Then, lesion-based damage will be computed as the proportion of lesioned voxels per ROI based on the lesion mask. Connectome-based damage (bottom row) will be computed as the number of diffusion tensor imaging (DTI) tracts that connect each pair of ROIs (tractography for reconstructing tracts will be performed guided by the white matter probabilistic map). **(C)** For each individual, three feature sets (lesion features, connectome features, and combination features) will be generated from the corresponding features after feature selection. **(D)** For each feature set, a “training cohort” will be used to build an optimal model based on a 10-fold cross-validation, and the prediction performance of the optimal model will be tested with the “test cohort” using ROC curve. **(E)** Then, three optimal models will be generated based on different feature sets (the lesion feature set for voxel model, the connectome feature set for connectome model, and the combination feature set for combination model). The prediction performance of each model will be compared, and the best-performing model will be selected.

Images from four sites (four hospitals) will be randomly partitioned into four equal portions. Approximately three-quarters of these images will be used as a “training cohort,” and the remaining one-quarter of these images will be used as a “test cohort.” In the “training cohort,” the proportion of lesioned voxels in the ROI and the links of the connectome matrix that are not shown difference between absence of communication impairment group and communication impairment group will be excluded, where the significance level is defined as *P* < 0.05 without multiple comparison correction in the two-sample test. The selected features will be used to define models predicting presence or absence of communication impairment in children with BCP. For each prediction model, 10-fold cross-validation (CV) will be used to evaluate the performance. This means that the “training cohort” will be divided into a training (nine folds) and a validation dataset (one fold), leaving 9 of 10 participants in the training dataset and the remaining participants in the testing dataset. For the training cohort, the various hyperparameters within each algorithm will be used to determine the prediction model. Then, the model will be applied to the validation dataset to predict children with the presence or absence of communication impairment (predicted label). The same procedure will be repeated with each of the one-fold participants or the left-out participants in the leave-one-out procedure, serving as the validation dataset for 10 iterations. Thus, each subject will receive a predicted label, and the accuracy of predictive model will be evaluate by comparing predicted labels to true labels of BCP children. The CV step will be repeated 100 times with random cohort designation to select the model with the best prediction accuracy. The whole “training cohort” will be reused in its entirety to retrain the model based on the classification algorithm and hyperparameters of the prior selected model. Then, the retrained model will be used to evaluate the “test cohort,” and the communication performance of every subject of the “test cohort” will be predicted by the model. The final accuracy of the prediction model will be defined by comparing predicted labels to true labels of BCP children in the “test cohort,” The Receiver Operating Characteristic (ROC) curve and the area under curve (AUC) will be calculated to evaluate the predictive ability of built models. A two-sided Hotelling-Williams test (Steiger, 1980) will be used to determine whether the multimodality prediction model is more accurate than any of the single-modality prediction models. *P* values < 0.05 will be considered indicative of statistically significant differences across models. Given the possible effects of age on imaging measures, the “test cohort” will be divided into three groups: younger (6–12 months), middle-aged (12–18 months), and elderly (18–24 months years), according to their age at MRI scan. The optimal model will be applied to all subgroups to exam whether the prediction accuracy changes with age at MRI scan.

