### Models for Predicting Communication Impairment

#### Preselection of Predictive Features

Since the number of streamlines between two cortical regions is averaged, the connectivity matrix is symmetrical with respect to the diagonal, and only the lower triangular matrix will be used for further analyses. For both lesion-based and connectome-based analyses, the feature set will include hundreds to thousands of feature vectors, and such high-dimensional data can cause the “curse of dimensionality.” To reduce the number of potential features introduced into the predictive model, a preselection procedure will be performed to exclude noisy or uninformative predictors from being fed into the prediction model, which can reduce the chance of model overfitting. First, for lesion-based analyses, only gray matter regions that are lesioned in more than 10% of the patients will be entered into the analysis. Second, for the links in the connectome matrix-based analyses, only those that are present in more than 75% of the patients will be entered into the analysis. After the above steps, each subject will have three feature sets: the lesion feature set, connectome feature set, and combination feature set.

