#### Development and Validation of Prediction Models

According to previously reported literature, for children with CP, the distribution of their CFCS grades is unbalanced and skewed. None or mild communication impairment (CFCS level I, II, III) in children with CP and PWMLs is more common than in those with severe communication impairment (CFCS level IV, V) (Kristoffersson et al., 2020). Such an imbalance distribution will cause misprediction during the process of predictive model generation (Saethang et al., 2016). Thus, we defined individuals who communicate at CFCS level I (defined as “effective sender and receiver communication with unfamiliar and familiar partners”) as having an absence of communication impairment. Patients with CFCS level I will be classified into the absence of communication impairment group, and those with CFCS levels II, III, IV, and V will be classified into the communication impairment group. In this way, the CFCS grade will be converted to a binary indicator, and our study will focus on identifying whether children with BCP have any communication impairment and improving the efficacy of the predictive model. All the variables will be centered and standardized before being entered into each model, which will be created with machine learning algorithms. In machine learning, the no-free-lunch theorem states that there is no one model (or, more generically, machine learning tool) that will work best for every problem (Wolpert and Macready, 1997). Therefore, several classification algorithms with varying hyperparameters will be evaluated using support vector machine, random forest, logistic regression, and other methods to investigate which algorithm will outperform competing approaches across all settings. The workflow of data processing and communication prediction is outlined in Figure 2. The detailed model building and validation steps are as follows.

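### The outcome-based P<0.05 feature screen is run once before cross-validation and its cut-off is never varied, so model choice for the connectome sets is unreliable and AUC can be lost

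*Protocol article*

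**What the plan says.** The procedure is in the protocol article under Development and Validation of Prediction Models, in the paragraph after Figure 2. Within the training cohort (about three-quarters of the images), lesion proportions and connectome links "that are not shown difference between absence of communication impairment group and communication impairment group will be excluded". The criterion is fixed: "the significance level is defined as *P* < 0.05 without multiple comparison correction in the two-sample test".

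The surviving features then define the models, and 10-fold cross-validation follows. What it varies is the algorithm, "evaluated using support vector machine, random forest, logistic regression, and other methods", and the settings inside each algorithm: "the various hyperparameters within each algorithm will be used to determine the prediction model". The final choice rests on that cross-validation: "The CV step will be repeated 100 times with random cohort designation to select the model with the best prediction accuracy". The chosen model is refitted on the whole training cohort and applied once to the test cohort.

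The screen therefore comes before the folds are formed, and its cut-off is not among the quantities varied. The legend of Figure 2 has the same order, with feature selection (C) ahead of cross-validation (D).

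**The concern.** Two features of this step work together.

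- **Order.** The screen uses the outcome labels of every training child, including those who later serve as the held-out fold. Features kept because they happen to separate the groups in the whole cohort will also separate them in each held-out fold. Repeating the cross-validation 100 times reshuffles the folds but leaves the screened set unchanged, so it does not help.
- **Fixed cut.** One marginal P value decides what every algorithm sees. If few links carry signal, 0.05 lets in many noise links. If very many links carry tiny effects, it discards most of them.

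At stake is the choice of algorithm and hyperparameters for the connectome and combination models. If cross-validation looks excellent for every candidate, it cannot separate one that copes with noise links from one that does not. The model taken to the test cohort may then be poorer than the data allow, and a usable MRI signal may be reported as weak.

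**Working it through.** **1. The plan's own figure.** Inputs from Sample Size: f² = 0.10, 6 predictors, α = 0.05, power 0.80. A noncentral F test with λ = f² × N and degrees of freedom 6 and N − 7 gives N = 143 (power 0.801), as stated. Dropout: 143 / 0.80 = 178.75, so 179 if rounded up against the stated 178, which does not matter here. The plan gives no expected AUC and no signal structure, so it has no AUC figure to reproduce.

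**2. Counts.**
- Training children: 0.75 × 143 = 107 (0.75 × 178 = 133 without dropout).
- Links from 122 regions: 122 × 121 / 2 = 7,381, before the 75% presence filter.
- Chance survivors at 0.05: 0.05 × 7,381 = 369. If the presence filter left 3,690 links: 185. For 122 lesion features: 6.

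**3. Effect of the order.** Ridge classifier, 107 training children, 50% impaired, independent Gaussian features, no signal; true AUC 0.50.

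| Features | CV AUC, screen before the folds | CV AUC, screen inside the folds |
|---|---|---|
| 2,000 | 0.99 | 0.54 |
| 122 | 0.72 | 0.48 |

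With 2,000 independent features and real signal, the pre-screened CV AUC was still 0.997 to 0.999 while the fitted model's true AUC was 0.56 to 0.73. With correlated features it was less extreme: 0.92, 0.94 and 0.89 in three patterns, against 0.76, 0.79 and 0.66 with the screen inside the folds, an optimism of 0.15 to 0.23. The plan selects on accuracy; these runs used AUC.

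**4. Why that matters for model choice.** True AUC with 2,000 features, 8 replicates, fixed 0.05 cut → tuned cut:

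| Assumed signal | L1 logistic | Random forest | Linear SVM |
|---|---|---|---|
| 3 features, d = 1.0 | 0.843 → 0.846 | 0.723 → 0.798 | 0.641 → 0.831 |
| 5 features, d = 0.8 | 0.817 → 0.821 | 0.673 → 0.746 | 0.666 → 0.786 |
| 500 features, d = 0.15 | 0.645 → 0.637 | 0.663 → 0.636 | 0.673 → 0.788 |

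At the fixed cut in the first row, L1 logistic regression beats linear SVM by 0.843 − 0.641 = 0.20. A cross-validation that is near its ceiling for the wrong reason cannot be relied on to find that difference.

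**5. Whole procedure.** With ridge and L1 models competing in cross-validation (107 training children, 16 replicates per assumed signal), tuning the cut with the screen inside the folds beat the written procedure by 0.04 to 0.21 true AUC for connectome-sized sets with signal. The difference was about 0.01 or less at 122 features or with no signal. Most of the sparse-signal gain came from moving the screen into the folds; tuning the cut alone added 0.00 to 0.09.

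**6. Cut-off alone, one algorithm at a time.** Ridge, 2,000 features, 30 replicates, tuned minus fixed:
- 3 features d = 1.0: +0.19
- 5 features d = 0.8: +0.13
- 20 features d = 0.5: +0.02
- 100 features d = 0.3: −0.02
- 500 features d = 0.15: +0.07
- 2,000 features d = 0.08: +0.14
- 122 features: −0.02 to +0.04

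A separate ridge run (3,690 links, 47% impaired, 40 replicates) gave +0.21 for 3 links at d = 1.0, +0.18 for 8 links at d = 0.8, +0.04 for 30 links at d = 0.5 and −0.01 for 200 links at d = 0.3. Another simulation of the 200-link pattern gave +0.08, so no weight is put on that pattern. The lowest value seen anywhere was about −0.03 (random forest, 500 weak features).

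**The case against.** The strongest reply is that a prespecified screen is a legitimate choice. It limits analyst freedom, and the held-out test cohort still gives an honest AUC for whichever model is built. That stands: a reader might infer that the reported test AUC is inflated, but this step does not inflate it. The damage is to model selection.

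Three stronger readings also fail.

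- A reader might infer that the plan tunes everything except this cut. It does not. Two further feature cuts are fixed: "only gray matter regions that are lesioned in more than 10% of the patients will be entered into the analysis" and, for links, "only those that are present in more than 75% of the patients will be entered into the analysis". Only settings within each algorithm are varied.
- A reader might say that the screen defeats its own stated purpose. The phrase "which can reduce the chance of model overfitting" belongs to those two prevalence cuts under Preselection of Predictive Features; the protocol states no such purpose for the P<0.05 step.
- A reader might state a definite AUC loss, for instance 0.1. No such figure follows from the documents. Size and sign depend on signal and algorithm, and 0.1 is neither a bound nor a typical value.

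It is also fair that 369 is a ceiling, that the lesion model is barely affected, and that the test cohort could not show the gain clearly. With 143 / 4 ≈ 36 children, split 17 and 19, the Hanley-McNeil variance at AUC 0.75 is [0.1875 + 16 × (0.600 − 0.5625) + 18 × (0.643 − 0.5625)] / (17 × 19) = 0.0069, a standard error of about 0.08. That limits what the trial can demonstrate. It does not justify selecting the model on a misleading criterion.

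**Conclusion.** The point holds in conditional form. As written, an outcome-based screen on the whole training cohort precedes the cross-validation that chooses the model, and its cut-off is never varied. For the connectome and combination sets, that cross-validation is too optimistic to be a reliable basis for choosing among algorithms and hyperparameters.

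The consequence is a possible true AUC lower by roughly 0.04 to 0.2 where signal exists, and about nil for the lesion set or without signal. Once the screen is inside the folds and algorithms are compared, the fixed cut by itself accounts for 0.00 to about 0.09.

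These sizes rest on assumed signal patterns, Gaussian features, 107 training children, 47% to 50% impaired, and 8 to 40 replicates per setting. The whole-procedure comparison used two penalised models, not the plan's full list. The ordering problem follows from the text and needs none of these assumptions.

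**What to change.** Amend the paragraph after Figure 2 so that:

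1. the two-sample screen is recomputed within each set of nine training folds, in every one of the 100 repeats, and never uses the held-out fold;
2. the screening cut-off, with no screen as one option, is one more hyperparameter, chosen in the same cross-validation as the algorithm and its settings;
3. the chosen cut-off is re-applied to the whole training cohort when the model is retrained, and the test cohort stays untouched until then.

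Tuning the cut without item 1 would carry the same bias, so the two must go together.

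The cost is wording and computing time; recruitment, imaging and outcome assessment do not change. The statistical downside is tuning noise of up to about 0.03 AUC if P<0.05 was already a suitable cut.

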### Secondary Aims

(1)To establish a practical method for multivariate lesion- and connectome-based approaches of children with BCP and PWMLs.(2)To identify injuries to cortical regions and connectomes associated with communication impairment in children with BCP with PWMLs.

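### The outcome-based P<0.05 feature filter is run once on the whole training cohort before the 10-fold cross-validation, so the cross-validated accuracy that selects algorithm and hyperparameters is biased upward

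*Protocol article*

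**What the plan says.** The steps are fixed in the protocol article, Development and Validation of Prediction Models (the paragraph after Figure 2), in this order.

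- In the training cohort, lesion proportions and connectome links that do not differ between impaired and unimpaired children are removed. The threshold is P<0.05, and the survivors go forward to the models: "without multiple comparison correction in the two-sample test. The selected features will be used to define models predicting presence or absence of communication impairment".
- Then, "For each prediction model, 10-fold cross-validation (CV) will be used to evaluate the performance", with the training cohort cut into nine folds for fitting and one for validation.
- "The CV step will be repeated 100 times with random cohort designation to select the model with the best prediction accuracy". The chosen algorithm and hyperparameters are refitted on the whole training cohort and applied to the test cohort, where final accuracy, ROC curve and AUC are obtained.

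The Figure 2 legend gives the same order: in panel C the three feature sets "will be generated from the corresponding features after feature selection", and 10-fold cross-validation follows in panel D. Nothing in the article says that the filter is repeated within folds. On the number of candidates, Preselection of Predictive Features says "the feature set will include hundreds to thousands of feature vectors" before two outcome-blind filters (regions lesioned in more than 10% of patients, links present in more than 75%).

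**The concern.** Cross-validation estimates performance honestly only if the left-out children had no part in building the model that predicts them. Here their outcome labels did: the group comparison that picks the features uses every training child, including the tenth later set aside. Features that separate the groups by chance in the full training cohort will also separate them in each left-out fold, so the score looks good even without any association.

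Two uses of that score are at stake. The article uses it to evaluate performance inside the training cohort, and to choose between support vector machine, random forest, logistic regression and other methods. Finding the algorithm that outperforms the others is a stated purpose of the section. If the inflation differs between algorithms, the comparison is not a fair one.

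**Working it through.** **Inputs.** From Sample Size: 143 evaluable children, 178 enrolled, 47.0% with communication abnormality in the cited cohort. From Development and Validation: about three-quarters go to training. From Lesion (Voxel)-Based Analysis: 122 atlas regions.

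**The plan's own figure.** A multiple-regression omnibus F test with f² = 0.10, 6 predictors, α = 0.05 and noncentrality 0.10 × N gives N = 143 (power 0.801). For dropout, 143 / 0.80 = 178.75, against the stated 178. The sample size is reproduced. The article states no cross-validated accuracy to reproduce.

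**Derived quantities.**
- Training cohort: 0.75 × 143 = 107.25, so 107; or 0.75 × 178 = 133.5, so 133 if nobody drops out.
- Candidates: at most 122 lesion features and at most 122 × 121 / 2 = 7,381 links. This is an upper bound, because the 75% presence filter and the restriction to gray matter regions reduce it.
- Null features expected to pass P<0.05: 0.05 × 122 = 6.1 lesion features; 0.05 × 7,381 = 369 links.

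**Null simulation.** The outcome is unrelated to every feature. The t-test filter at P<0.05 is run either once on all training children (as written) or afresh in each set of nine folds; 10-fold cross-validation follows, with an independent test set alongside. There were 30 runs per setting for ridge and nearest centroid, and 8 for linear and RBF support vector machine, logistic regression and random forest. Correlated features came from 5 to 30 latent factors carrying 50% or 80% of the variance.

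| Candidates (n = 107, 47% impaired) | Cross-validated accuracy, filter before folds |
|---|---|
| 60 independent | about 0.62 |
| 122 independent | 0.61-0.68 |
| 122 correlated | 0.585-0.666 |
| 1,000 independent | 0.85-0.91 |
| 3,000 independent | 0.96-0.99 |
| 7,381 independent | 0.999-1.00; random forest 0.82 |
| 7,381 correlated | 0.56-0.81 |

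With the filter inside the folds, accuracy was 0.48-0.55 in all settings at this prevalence; independent test accuracy was 0.46-0.53. With n = 133 the biased figures were 0.65-0.67 at 122 features and 0.998-1.00 at 7,381 independent links.

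**Does the inflation differ by algorithm?** Yes. On the same independent noise with 7,381 links, linear support vector machine and logistic regression scored 1.00 and random forest 0.82, while true accuracy was 0.49-0.51 for all of them. The leak alone creates a gap of 0.18. On correlated noise (20 factors, 50% of variance) the gap was 0.812 − 0.704 = 0.108.

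**With a real signal** (122 features, 20 shifted by 0.4 SD): filter before folds 0.75-0.82, inside folds 0.67-0.70, independent test 0.69-0.71. The inside-fold figure is close to the truth; the other is not.

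**What does it cost the chosen model?** A separate simulation with real signal (n = 107, 47% impaired, effect 0.4 SD on 2-17% of features, 21 kernel-ridge and centroid candidates, no random forest) compared the true test accuracy of the model selected under each scheme, filter before versus inside the folds:
- 60 features: 0.645 vs 0.639
- 122 features: 0.697 vs 0.692
- 1,000 features: 0.767 vs 0.767 (correlated 0.774 vs 0.784)
- 3,000 features: 0.752 vs 0.764 (correlated 0.810 vs 0.820)
- 7,381 features: 0.763 vs 0.781

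The largest loss is 0.781 − 0.763 = 0.018. The model chosen on the biased score still beat the average candidate (0.62-0.69).

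**The case against.** The best defence is that the result which counts is clean. The article takes final accuracy and AUC from the test cohort, which the filter never sees, and does not name cross-validated accuracy as a headline result. The final features are also the same under either scheme, because the filter is in any case run on the full training cohort before retraining; only the choice of algorithm and hyperparameters can change. An uncorrected threshold is a legitimate lenient screen for prediction. All of this stands and limits the severity. It does not remove the bias in a score that the article uses to evaluate performance and to pick the algorithm.

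A reader might infer more than the document supports:

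- *That cross-validated accuracy will approach 100% whatever the data.* This needs several thousand nearly independent links. It does not hold for the lesion set, for random forest, or for correlated links, and links that share regions are plausibly correlated.
- *That model choice becomes noise.* The simulations with real signal show a slightly degraded choice.
- *That the procedure favours the connectome and combination sets.* Figure 2 runs cross-validation separately within each feature set, and the abstract and the Development section compare the resulting models in the test cohort.
- *That the best single run of 100 is taken.* The sentence can equally mean the model that does best across the repeats.
- *That Aim 2 will be answered with the uncorrected list.* Secondary Aims promise "To identify injuries to cortical regions and connectomes associated with communication impairment", but the article describes the filter only as a step before modelling and does not say that its survivors are the Aim 2 result.
- *That the 10% and 75% filters, standardisation and ComBat share the fault.* As described, none uses the outcome, and no calculation here shows that they cause the bias.

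**Conclusion.** The point holds in this limited form and should be fixed. As written, the cross-validated accuracy is optimistically biased because outcome labels from the left-out fold enter feature selection. On noise, against a true value of about 0.50, the bias is about 0.11 to 0.18 for 122 independent lesion features, about 0.06 to 0.31 for 7,381 correlated links, and up to about 0.50 for several thousand near-independent links (0.32 for random forest at 7,381).

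These sizes assume 107 training children, 47% impaired, and the correlation structures tried. The article states neither the surviving link count nor the correlation, so no single figure can be given. Because the inflation differs by algorithm, the score is an unreliable basis for the algorithm comparison and must not be read as performance. The test-cohort accuracy and AUC, and the comparison of feature sets made there, are not contaminated. The expected loss in the selected model's true accuracy is about 0-2 points under the candidates simulated, which did not include random forest.

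**What to change.** In Development and Validation of Prediction Models, and in Figure 2 panels C and D, state that:

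1. the P<0.05 filter, with standardisation alongside it as good practice, is refitted within each set of nine training folds and applied unchanged to the left-out fold;
2. algorithm and hyperparameters are selected on mean out-of-fold performance over the 100 repeats, which also settles the ambiguous sentence;
3. the filter is then rerun on the full training cohort for the final retraining;
4. performance claims rest on the test cohort only.

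If regions or links passing the uncorrected filter are to be reported for secondary Aim 2, report them with false-discovery-rate control.

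The cost is a few sentences and more computing time. Training accuracies will look less favourable. Data collection and the test-cohort analysis do not change.

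### The Hotelling-Williams test named for comparing the models tests equality of correlations, not the label accuracy or AUC by which the protocol measures performance

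*Protocol article*

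**What the plan says.** All of this stands in the protocol article, section Development and Validation of Prediction Models, including the text after Figure 2.

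- **Outcome.** CFCS level I is set against levels II to V: "In this way, the CFCS grade will be converted to a binary indicator". Classification algorithms (support vector machine, random forest, logistic regression and others) are fitted to it.
- **Accuracy.** "The final accuracy of the prediction model will be defined by comparing predicted labels to true labels of BCP children in the" test cohort, which is one quarter of the images.
- **Discrimination.** "The Receiver Operating Characteristic (ROC) curve and the area under curve (AUC) will be calculated to evaluate the predictive ability of built models".
- **Model comparison.** "A two-sided Hotelling-Williams test" at P < 0.05 "will be used to determine whether the multimodality prediction model is more accurate than any of the single-modality prediction models".

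The abstract also promises a statistical comparison of prediction accuracy across models in the test cohort. No other test for that comparison is named, and no correlation between prediction and outcome is defined anywhere as a measure of performance.

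**The concern.** The Hotelling-Williams test has as its null hypothesis that two correlations sharing one variable are equal: r(outcome, prediction 1) = r(outcome, prediction 2). Its reference distribution assumes joint normality. It suits a study that predicts a continuous score.

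Here the outcome is binary and the two stated measures are the proportion of correct labels and the AUC. Equal accuracy does not imply equal label correlation (phi), and equal AUC does not imply equal correlation of scores with the outcome. Phi is also undefined if a model puts every child in one class.

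At stake is the statement that combining lesion and connectome features predicts better than either alone. It would rest on a P value for a quantity the study does not report, with a false-positive rate that may be well above 5%.

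**Working it through.** **The plan's own figures.** The protocol gives no figure for the model comparison. Its sample size concerns a different analysis, a regression F test with f² = 0.10, 6 predictors, α = 0.05 and power 0.80. The noncentral F calculation (λ = f²N, df 6 and N − 7) reproduces N = 143, with power 0.801. Dropout of 20% gives 143/0.80 = 178.75, against 178 stated. The test cohort is one quarter: 178/4 = 44.5 if all are retained, 143/4 = 35.75 if only completers. So n is about 36 to 44.

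**Assumed, because the documents give none.** Accuracies of 0.60 to 0.90; correlation of the two models' errors 0.5; prevalence of impairment 60%, inside the 46-78% range in the Introduction.

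**Step 1: the test.** With outcome 1 and predictions 2 and 3,

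t = (r12 − r13) √{ (n−1)(1+r23) / [ 2·(n−1)/(n−3)·|R| + r̄²(1−r23)³ ] }, df = n − 3,

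where |R| = 1 − r12² − r13² − r23² + 2·r12·r13·r23 and r̄ = (r12 + r13)/2. On trivariate normal data this rejected 5.0-5.2% under the null, so the implementation is sound.

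**Step 2: equal accuracy, unequal correlation.** Take 44 children, 34 impaired and 10 not.
- Model 1, 7 false negatives and 1 false positive: accuracy 36/44; phi = (27×9 − 7×1)/√(34×10×28×16) = 236/390.3 = 0.605.
- Model 2, 1 false negative and 7 false positives: accuracy 36/44; phi = (33×3 − 1×7)/√(34×10×40×4) = 92/233.2 = 0.394.

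The two accuracies are identical, but the quantities the test compares are not. (In this one data set P = 0.21; the example shows the mismatch, not a false positive.)

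**Step 3: why the error rate rises with accuracy.** Under normality the variance of r is about (1 − r²)²/n. For balanced labels with sensitivity = specificity = a, phi is about 2a − 1, with variance about 4a(1 − a)/n = (1 − phi²)/n. The normal formula is too small by the factor 1/(1 − phi²): 1/(1 − 0.2²) = 1.04 at a = 0.60, 1/(1 − 0.6²) = 1.56 at 0.80 and 1/(1 − 0.8²) = 2.78 at 0.90. The factor does not involve n.

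**Step 4: simulated rejection with truly equal accuracy** (labels, sensitivity = specificity, prevalence 60%, error correlation 0.5):

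| Accuracy | Williams n=36 | Williams n=44 | McNemar n=36 | McNemar n=44 |
|---|---|---|---|---|
| 0.60 | 6.0% | 5.9% | 2.4% | 2.7% |
| 0.70 | 8.3% | 7.8% | 2.1% | 2.4% |
| 0.80 | 15.3% | 14.5% | 1.8% | 2.2% |
| 0.90 | 34.4% | 34.6% | 0.9% | 1.2% |

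At n = 142 the Williams rate is still about 14% at 0.80 and 31-32% at 0.90. At accuracy 0.80 and n = 44 it is 13-16% across prevalence 46-78%.

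**Step 5: equal accuracy, different balance of errors.** Prevalence 78%, both accuracies 0.80. One model has sensitivity and specificity 0.80 (phi 0.53). The other has about 0.95 and 0.27 (0.78×0.95 + 0.22×0.27 ≈ 0.80; phi 0.30). Williams rejects 33% (n = 36) and 36% (n = 44); exact McNemar rejects 2%.

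**Step 6: continuous scores with equal AUC of 0.80.** At n = 36 and 44, Williams rejects 4-5% when both scores are normal on one linear scale, 6-8% after a logistic transform, and 21% and 28% when one score is on an exponential scale. DeLong rejects 4-5% throughout.

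**The case against.** The protocol does not say whether the test is to be run on labels or on continuous scores, and a ROC curve needs scores. On roughly normal scores with a common scale the test holds its level, and on labels at accuracy near 0.60 it is close to 5%. This stands. A reader might infer that the test gives wrong answers for any binary outcome, and the documents do not support that. But nothing in the protocol secures the favourable case: accuracy is defined on labels, and the algorithms listed need not produce scores on one scale.

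A reader might also infer that the test badly misses real differences in accuracy. With true accuracies of 68% and 79% at equal AUC and 78% prevalence, it rejects 11-12% against 57-61% for McNemar, but only at n = 142. At n = 36 the figures are about 10-12% and 12-14%. Moreover, calling every child impaired already scores 78% there, so the gain is a shift of cut-off and not better prediction. The loss-of-power argument does not hold at the protocol's test-cohort size.

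Finally, the primary aim is to develop and validate a model, not to show that the combined one is superior; Figure 2 selects the best-performing model without stating a P value condition, and accuracy and AUC will be reported regardless. That limits the damage. The abstract nevertheless presents the comparison as part of the study, and the test is fixed in the text, so it is not a detail left to an analysis plan.

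**Conclusion.** The point holds: the test named does not match either performance measure the protocol defines. On labels with equal accuracy its false-positive rate is about 5-8% at accuracy 0.60-0.68, 14-16% at 0.80 and 33-36% at 0.90, for 36 to 44 test children and a nominal 5%. More children do not remove the excess. On scores it can be near nominal or, if scales differ, 21-28%.

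These sizes rest on assumed accuracies, prevalence, error correlation and score scales. The mismatch itself rests only on the protocol's text. The inflation is worst at the accuracies a clinically useful model would need.

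**What to change.** Replace the Hotelling-Williams sentence in Development and Validation of Prediction Models with paired tests on the held-out test cohort:

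- the AUC difference by the paired DeLong test or a paired bootstrap, as the main comparison;
- label accuracy by the exact McNemar test, in support;
- the combination model called better only if it beats both the lesion model and the connectome model. Because both comparisons must succeed, this rule needs no adjustment of α.

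Keep the comparison on the test cohort. Moving it to out-of-fold predictions from all completers would give up the promised held-out evaluation. It would also risk leakage from the outcome-based feature filter and the model selection unless every step were nested.

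The cost is one sentence and standard software, and the sample size does not change. The downside should be stated: with about 36 to 44 test children these tests have low power (McNemar about 12-14% at n = 36 and 18% at n = 44 in the 68% versus 79% scenario). Report each difference with a confidence interval, and do not read a non-significant result as equality.
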